## Abstract

**Background:**

China has the largest burden of primary angle-closure glaucoma (PACG) worldwide. The mechanism of the angle closure is complex and includes pupillary block and non-pupillary block. Currently, opinion is that laser peripheral iridotomy (LPI) alone is not sufficient to prevent disease progression. Laser peripheral iridoplasty (LPIP) is an alternative and effective way of widening the angle recess in eyes that are affected by primary angle closure (PAC). However, it is not known if greater benefit would be achieved using LPI plus LPIP for PAC with multiple mechanisms (MAC). Thus, the aim of this study is to demonstrate if LPI plus LPIP would be more effective than single LPI in controlling the progression of PAC with multiple mechanisms, based on ultrasound biomicroscopy (UBM) classification. A secondary aim is to determine whether or not this would result in the use of less medication and/or prolong the time to antiglaucoma surgery.

**Methods:**

This multiple-mechanism angle-closure study will comprise a 3-year, multicenter, randomized, parallel-group, open-label, superiority trial, the aim of which will be to evaluate the safety and efficacy of LPI plus LPIP versus LPI for PAC. It is anticipated that 240 adults, diagnosed with PAC (the mechanism of angle closure will be assessed by UBM and it will be determined whether or not it involves multiple mechanisms) will be recruited from ten ophthalmic centers in China. Participants will be randomly allocated to receive either single LPI or LPI plus LPIP. Participant assessment will be designed to test the rate of disease progression and who will be followed up for 3 years. The primary outcome will be the disease progression rate and a comparison will be made between the LPI and LPI plus LPIP groups using Pearson’s χ^2^ test. Logistic regression analysis will be performed to account for the central effect.

**Discussion:**

If the LPI plus LPIP is found to significantly decrease the rate of PAC progression, this intervention could potentially be a standard therapy to be used to treat PAC when multiple mechanisms are involved in angle closure. Subsequently, this would have the potential to delay the rate of PAC progression to PACG and delay the time to the administration of antiglaucoma medication or trabeculectomy surgery.

**Trial registration:**

ClinicalTrials.gov, NCT02613013. Registered on 24 November 2015.

In fact, the study was due to start in late October 2015, however, there were no patients recruited in October, and when we registered at ClinicalTrials.gov on 5 November 2015, we received suggestions on the English translation of our protocol from the PRS Team at Clinicaltrial.gov, so the final successful registration date was on 24 November 2015.

**Electronic supplementary material:**

The online version of this article (doi:10.1186/s13063-017-1860-4) contains supplementary material, which is available to authorized users.

## Background

Glaucoma is the second leading cause of irreversible blindness and it is estimated that there will be 79.6 million glaucoma patients globally by 2020. Although angle-closure glaucoma (ACG) only accounts for 26% of all glaucoma, it is expected that angle-closure glaucoma will affect 87% of Asian glaucoma patients, with bilateral blindness recorded in 5.9 million people with ACG [1]. It was found in a population-based study that China has the largest burden of primary angle-closure glaucoma (PACG) in the world [2].

Laser peripheral iridotomy (LPI) is the suggested initial treatment for primary angle closure (PAC) and early PACG as it eliminates pupillary block, allowing the convex iris to flatten, while widening the anterior chamber angle [3]. However, the pathophysiological features that underlie PAC are complex and include pupillary block and non-pupillary block mechanisms [4].

It was found in our previous ultrasound biomicroscopy (UBM)-based study that multiple mechanisms of angle closure were found in approximately 55% of PACG patients. The causes of the angle closure include pupillary block leading to peripheral iris bombe, anterior rotation of the ciliary body, and a thickened and anteriorly located peripheral iris [5]. Therefore, LPI alone may not be effective in angle closure caused by multiple mechanisms.

It was discovered in the Liwan Eye Study and Zhongshan Angle-Closure Prevention Trial that approximately 20% of Chinese eyes with suspected PAC had residual angle closure after single iridotomy and the greater angle width following iridotomy further decreased as time went on [6, 7]. Choi et al*.* followed up eyes with peripheral anterior synechia (PAS) after LPI for a mean of 34.4 months and found that disease progressed in 32% of the eyes due to the existence of a non-pupillary block component in angle closure, i.e., plateau iris [8]. It was shown in a 2-year follow-up study on primary angle closure suspects (PACS) after LPI that roughly 28% of the patients progressed to PAC. A decreasing anterior chamber area was predictive of progression from PACS to PAC [9].

Contraction burns to the peripheral iris result from peripheral iridolasty, leading to contraction of the peripheral iris stroma and the creation of a space between the anterior iris surface and the trabecular meshwork [10]. It has also been suggested that this effectively opens up the appositionally closed portions of the drainage angle, even resulting in a synechiolysis effect [11]. Ritch et al*.* found that laser peripheral iridoplasty (LPIP) was highly efficient in eliminating residual appositional closure following LPI caused by plateau iris [12].

Therefore, it is reasonable to hypothesize that LPI plus LPIP would be more efficacious in opening up the angle closure caused by multiple mechanisms and would provide greater intraocular pressure (IOP) control. It was found in our previous randomized controlled trial that LPI plus LPIP resulted in superior reduction in the PAS surface area than LPI alone in synechial PAC and PACG after 1-year follow-up, although a similar magnitude of IOP reduction was reported for the two interventions [13]. However, to our knowledge, a guideline has not been published, nor have any studies been conducted, on the treatment of PAC based on the clinical research associate classification of various mechanisms of angle closure.

## Methods

### Study objective

The aim of this study is to demonstrate the efficacy of LPI plus LPIP versus LPI in reducing the rate of 3-year disease progression in patients with multiple mechanisms of angle closure based on UBM classification. A secondary objective is to assess the safety of LPI plus LPIP in the study population over its duration.

### Trial design

This study has been designed as a 3-year, multicenter, randomized, parallel group, open-label, superiority trial. Interim analysis will not take place during this study. A completed Standard Protocol Items: Recommendations for Interventional Trials (SPIRIT) checklist for the trial is available (see Additional file 1).

### Participant characteristics

Patients from the ten ophthalmic centers in China will be assessed for suitability regarding participation in the study by the primary investigator at each center and by the researchers who confirm the UBM reading results, using the criteria detailed herein.

### Inclusion criteria

Inclusion criteria are as follows:Patients with a clinical diagnosis of PAC, with IOP ≤ 30 mmHg and PAS ≤ 270 °.Patients with PAC with multiple mechanisms based on the results of a UBM examination. (“Multiple mechanisms” is defined as PAC caused by pupillary block plus at least one non-pupillary block mechanism).Patients with visual acuity ≥ 20/40.Patients who are aged 40–75 years and of Chinese descent.

If both eyes of the patient are eligible for inclusion in the study, the one with greater diminished visual acuity will be selected. Only one eye per patient will be eligible for inclusion in the study.

Eligible patients who are already on antiglaucoma medication will be required to undergo a polypharmacy washout before the randomization process is applied. Different washout periods apply to the various medications, for example, prostaglandin analogs are eliminated after 4 weeks, beta blockers after 3 weeks, adrenergic agonists after 2 weeks, and cholinergic agonists and carbonic anhydrase inhibitors after 5 days. The polypharmacy washout process will be stopped in patients with an IOP > 30 mmHg during the washout period and they will be withdrawn from the study.

A diagnosis of PAC will be based on the 2010 Glaucoma Preferred Practice Pattern® of eyes that are classified as having at least 180 ° of iridotrabecular contact and an elevated IOP (IOP ≥ 21 mmHg) on at least one occasion, with this result recurring three times, or PAS. Visual field loss and glaucomatous optic neuropathy, as defined herein, are exclusion criteria.

### Exclusion criteria

The exclusion criteria are as follows:Patients who are unwilling or unable to provide consent to participation in the study, who are unwilling to submit to the randomization process, or are unable to return for the scheduled protocol visits.Patients with angle closure due to secondary causes (i.e., subluxated lens, neovascular, uveitic, traumatic and postoperative).Patients who have undergone previous incisional intraocular surgery or ocular laser in the study eye (LPI, LPIP, cyclodestructive procedure, and cataract surgery).Patients with PAC with glaucomatous neuropathy.Patients who have a cataract in the study eye and who anticipate having cataract surgery in the next 3 years. (The existing cataract could affect the visual field and fundus examination and it is likely that visual acuity would be < 20/40 due to the existing cataract).Patients using IOP-lowing drugs who do not agree to submit to the medication washout process.Patients who require glaucoma surgery combined with other ocular procedures, such as cataract surgery, penetrating keratoplasty, and retinal surgery), or who anticipate the need for urgent additional ocular surgery.Patients with other coexisting ocular diseases, such as an abnormal cornea or a corneal infection, iridocorneal endothelial syndrome, anterior segment dysgenesis, nanophthalmos, high myopia (>6.0 D), chronic or recurrent uveitis, ocular cancer, trauma, central retinal vein occlusion, central retinal artery occlusion, and retinal detachment).Patients with a corneal endothelium count of < 1000/mm^2^.Patients who require the long-term use of local or systemic steroids.Patients who are unwilling to discontinue contact lens use after surgery.Patients who are participating in other clinical trials.Pregnant or nursing women.Patients with severe systemic disease, such as diabetes mellitus, hypertension, end-stage cardiac disease, nephropathy, respiratory disease, and cancer.Patients who are allergic to pilocarpine or alcaine.Patients with a contraindication to laser treatment for ocular disease.

### Recruitment procedure

The participant flow diagram is showed in Fig. 1.

**Fig. 1 Fig1:**
[figure not shown]
Participant flow diagram. *LPI* laser peripheral iridotomy, *LPIP* laser peripheral iridoplasty, *PAC* primary angle closure

### Sample size

The sample size calculations are based on published PAC disease progression with LPI and LPIP treatment. Disease progression is defined as glaucomatous optic nerve injury, increased IOP for which antiglaucoma drugs are required, and PAS progression according to the published clinical trials [13–15]. It is assumed that the 3-year PAC progression rate after receiving LPI will be approximately 55%, and the rate for LPI plus LPIP will be 35%, with 80% statistical power and a two-sided test at 5% significance. Thus, allowing for 20% loss to follow-up, a sample size of 240 participants for this study is required (calculated using nQuery Advisor® + nTerim® 3.0 software; Statsols, Boston, MA, USA). There will be 120 patients in each treatment arm. The anticipated number of patients in the study (240) will be recruited over a 12-month period.

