### Blinding

This study is an open-label trial.

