### Primary outcome measures

The PAC progression rate will be determined by the number of patients in whom the disease progresses following laser treatment in each group within the 3-year follow-up period. PAC progression is defined as the presence of any of the following:Acute angle-closure crisis.An IOP measurement taken 1 month after the laser procedure that is 8 mmHg higher than that recorded at treatment initiation.An IOP measurement taken 1 month after the laser procedure that is ≥ 22 mmHg when measured three times in succession.The progression of PAS ≥ 1 clock hour within 3 years of the laser procedure, as determined by gonioscopy.Glaucomatous neuropathy within 3 years of the laser procedure.

Acute angle-closure crisis is defined as:The presence of at least two of the following symptoms: ocular or periocular pain, nausea and vomiting, blurred vision, and multicolored halos around lights (an occasional symptom).An IOP measurement of at least 22 mmHg, as measured by Goldmann® applanation tonometry.The presence of at least three of the following signs: conjunctival injection, corneal edema, a mid-dilated unreactive pupil, and a shallow anterior chamber.

Glaucomatous neuropathy is defined as:The documented progression of diffuse thinning and focal narrowing or notching of the optic disc rim.A cup disc ratio of ≥ 0.6.A cup-disc asymmetry ratio of ≥ 0.2 for similar-sized eyes or optical discs.Diffuse or localized abnormalities in the peripapillary retinal nerve fiber layer.The presence of glaucomatous visual field defect, defined as reproducible visual field defects, including nasal step, arcuate field defect, or paracentral depression in the clusters of the test sites.Visual field loss in the upper hemifield that is different to that in the lower hemifield.The absence of any other known explanation.

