### Secondary outcome measures

Secondary outcome measures include the following:Determining, through the administration of a questionnaire, whether or not additional medication (to control IOP) or additional surgery is required to control the progression of PAC.Establishing whether or not there are any changes in the best-corrected visual acuity after the laser procedure.Determining the number of corneal endothelium cells.Establishing any change in the angle width and configuration, as measured by UBM.

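### The 55% and 35% planning rates rest on a definition that counts IOP rise needing drugs, but the primary outcome does not count added treatment, so a treated eye can be scored as a non-progressor

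*Protocol article*

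**What the plan says.** All references are to the protocol article.

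- **Sample size.** Planning rates of 55% and 35% are tied to a definition credited to published trials: "Disease progression is defined as glaucomatous optic nerve injury, increased IOP for which antiglaucoma drugs are required, and PAS progression". They are used "with 80% statistical power and a two-sided test at 5% significance", and "allowing for 20% loss to follow-up, a sample size of 240 participants for this study is required".
- **Primary outcome measures.** "PAC progression is defined as the presence of any of the following": acute angle-closure crisis; IOP 8 mmHg above the value at treatment initiation; IOP of 22 mmHg or more three times in succession; PAS progression of at least 1 clock hour; glaucomatous neuropathy. Starting medication and having surgery are not on the list.
- **Secondary outcome measures.** A questionnaire is to establish "whether or not additional medication (to control IOP) or additional surgery is required to control the progression of PAC".
- **Blinding.** "This study is an open-label trial".
- **Data analysis.** Progression at 3 years is compared by Pearson's chi-square test in the ITT and per-protocol populations. Last observation carried forward applies where the primary outcome is not available. Nothing is said about IOP readings taken after treatment has been added.

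**The concern.** The article gives two definitions of progression. Under the one behind the planning rates, an IOP rise that needs drugs is itself an event. Under the one to be tested, the same eye is an event only if it crosses a numerical threshold or meets another listed component.

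Added drops or surgery are meant to lower IOP. Once they are given, later readings say less about what the laser achieved, and a threshold not yet reached becomes harder to reach. In an open-label trial the decision to add treatment can depend on knowledge of the arm. If LPI-alone eyes are treated earlier or more often, a real benefit of the combination is diluted; if combination eyes are, the benefit is exaggerated. The chi-square comparison cannot tell these apart. The 80% power is also justified for an endpoint that is not quite the one tested.

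**Working it through.** **1. The plan's own figure.** Inputs from Sample size: p1 = 0.55, p2 = 0.35, two-sided 5%, power 80%, 20% loss. The pooled proportion is 0.45.

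n per arm = [1.96 × √(2 × 0.45 × 0.55) + 0.8416 × √(0.55 × 0.45 + 0.35 × 0.65)]² / 0.20² = [1.96 × 0.7036 + 0.8416 × 0.6892]² / 0.04 = 95.9, so 96.

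96 / (1 − 0.20) = 120 per arm, 240 in total. This matches the article, and power at 96 per arm is 0.800.

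**2. The two definitions side by side.**

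| Element | Sample size | Primary outcome |
|---|---|---|
| Optic nerve damage | yes | yes |
| PAS progression | yes | yes, at least 1 clock hour |
| IOP | rise that needs drugs | rise of 8 mmHg, or 22 mmHg or more three times in succession |
| Acute crisis | not named | yes |
| Added medication | part of the IOP element | no (secondary) |
| Added surgery | not named | no (secondary) |

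**3. The eye that falls between them.** Take an eye with one or two readings of 22 mmHg or more, a rise under 8 mmHg, and no crisis, PAS or nerve event. Drops are judged necessary. It has progressed by the planning definition but meets no primary component. If later IOP is lower because of the drops, it ends the trial as a non-progressor. Surgery can act in the same way, but that part rests on the primary and secondary outcome lists alone, since the planning definition names only drugs.

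**4. Can the effect on power be signed?** The article gives no rescue rate, so the rates below are assumptions, chosen to show the range. Power = Φ[(d − 1.96 × se0) / se1], where d is the difference in rates, se0 the pooled and se1 the unpooled standard error. It is shown for 96 evaluable per arm and for all 120, because ITT with carried-forward values is planned.

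| Assumed change to the planning rates | LPI vs combination | Power, 96 | Power, 120 |
|---|---|---|---|
| none | 55% vs 35% | 0.800 | 0.881 |
| 5 points lost in each arm | 50% vs 30% | 0.812 | 0.890 |
| 10 points lost in each arm | 45% vs 25% | 0.833 | 0.906 |
| 10% of events lost in each arm | 49.5% vs 31.5% | 0.723 | 0.815 |
| 20% of events lost in each arm | 44% vs 28% | 0.638 | 0.736 |
| 5 points lost with LPI, 2.5 with combination | 50% vs 32.5% | 0.695 | 0.790 |
| 2.5 points lost with LPI, 5 with combination | 52.5% vs 30% | 0.892 | 0.948 |
| 5 points gained in each arm (added components) | 60% vs 40% | 0.796 | 0.877 |

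Power moves either way depending on the assumption, so no single figure can be defended. In the rows where the arms lose different numbers of points, the observed difference is itself biased, so higher power there is no advantage.

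**The case against.** Four points count against a stronger claim, and most of them stand.

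- *IOP is not ignored.* The primary outcome counts IOP rise by two fixed thresholds, and an event once met stays counted whatever is given afterwards. Many drug-treated eyes will be caught. A reader might infer that the patients who do worst are scored as successes. The article does not support that: crisis, an 8 mmHg rise, PAS progression and neuropathy all count, so the exposed eyes are intermediate ones treated early. If the three successive readings are taken at a single visit, which the wording does not exclude, the gap is narrower still.
- *The direction is unknown.* A reader might infer that power must fall below 80%, or that the benefit must be hidden. Neither follows from the article, which gives no rescue rate and whose primary outcome adds acute crisis and a specific 8 mmHg criterion. Nothing in it links IOP-lowering drops to less PAS progression, so the argument is confined to IOP.
- *The planning definition may only describe its sources.* Rates are often borrowed from trials with similar but not identical endpoints. That is fair, but the article applies the rates to its own outcome without saying that the definitions differ.
- *Rules for starting treatment and for scoring may sit in the full protocol.* The article does not say who starts drops or on what grounds, and that silence is not held against it. The disagreement between its two definitions, however, is in its own text.

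It is also fair that fixed thresholds are more objective than a treatment decision made without masking. That argues against simply moving added treatment into the primary outcome.

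**Conclusion.** The concern holds in limited form. The planning definition and the primary outcome differ on whether an IOP rise needing drugs is an event, and as written an eye treated before it meets a threshold can be scored as a non-progressor. In an open-label trial this may differ by arm.

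The size cannot be given: it depends on how many eyes are treated before a threshold is met, in which arm, and how many events the added components contribute. The 80% power is therefore not established for the endpoint tested, which is different from being shown to be too low. The sample-size arithmetic is correct. This should be fixed, with moderate confidence in its practical importance.

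**What to change.** 1. Reconcile the definitions in Sample size and Primary outcome measures, and re-justify 55% and 35% for the definition used. If the source trials used a different endpoint, say so and say how the rates were carried over.
2. State that IOP measured after added IOP-lowering medication or antiglaucoma surgery in the study eye does not count as evidence of non-progression.
3. Pre-specify an analysis of the primary outcome that counts such treatment as progression, taken from the Medication record and Antiglaucoma surgery rows of Table 1. Report it beside the analysis by the listed primary criteria alone.

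The cost is small. Table 1 already has medication recorded at every post-laser visit and antiglaucoma surgery from month 1, so no new data are needed. The drawback is that starting treatment is a judgement made without masking, which is why both analyses should be shown. Recruitment was under way, with more than a quarter of the sample enrolled, so the change should be dated and made without sight of outcome data by arm. It concerns scoring only and sets no rule for when to treat.

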### Randomization process

Patients will be randomly assigned to treatment with either single LPI or LPI plus LPIP using a 1:1 ratio via an online central randomization system. (This system is run by personnel in the Department of Biostatistics, Southern Medical University, Guangzhou, China), using the IOP as the stratification parameter. Patients will be stratified into a high IOP subgroup (21 mmHg to ≤ 30 mmHg) and a low IOP subgroup (≤21 mmHg) since it is likely that IOP will vary in the enrolled PAC participants. This procedure will ensure that there is a nearly equal number of patients in each treatment group early on in the trial and that the investigator will not be able to predict the next treatment assignment. In addition, the number of patients in the high and low IOP arms will almost be equal. The intervention date is the study entry date. Dates for all postoperative follow-up visits will be computed from this date.

